### Interventions

In step 1, the four arms of the intervention are AmBisome 10 mg/kg on day 1 (single dose), AmBisome 10 mg/kg on day 1, AmBisome 5 mg/kg on day 3 (two doses), AmBisome 10 mg/kg on day 1, AmBisome 5 mg/kg on days 3 and 7 (three doses), and AmBisome 3 mg/kg/d for 14 days, which will act as the control (Fig. 3). In step 2 where the interest is in clinical endpoints, the intervention will be use of the shortest-course AmBisome regimen tested in step 1 (either regimen 1, 2 or 3 above) meeting the predefined safety and efficacy criteria and selected by the Trial Steering Committee (TSC) for further study, and AmBisome 3 mg/kg/d for 14 days used as the control. Note that all patients also receive fluconazole 1,200 mg/d for the first 2 weeks, followed by 800 mg/d until 10 weeks, and 200 mg/d thereafter. ART will be commenced 4 to 5 weeks after initiation of antifungal therapy. The trial clinical team is not blinded to treatment allocation, however, laboratory personnel performing CFU counts are blinded to treatment allocation.

**Fig. 3 Fig3:**
[figure not shown]
Trial schema. Trial entry, randomisation and treatment. *ART* anti-retroviral therapy, *EFA* early fungicidal activity, *SAE* serious adverse event

### Rescue medication

All patients will receive fluconazole from day 1 at 1200 mg/d for the first 2 weeks, making it very unlikely that CSF CFU counts will rise after the day 3 LP [5, 6]. However, in view of the single-dose AmBisome arm and to ensure that all patients receive effective induction therapy, if CFU counts go up (by any amount) after day 3, i.e., on the day-7 or day-14 LP, then the patient will switch to daily AmBisome (3 mg/kg/d) for 7 to 14 days and until the CSF is sterile. Thus, all patients will be ensured effective induction therapy.

### Schedule

Clinical response will be monitored daily for the first 2 weeks or until discharge (whichever is later), then on follow up at 3, 4, 6 and 10 weeks after the start of therapy. Every effort will be made (e.g., with mobile telephone calls and financial help with travelling expenses) to obtain accurate and complete follow-up data for 10 weeks after the start of treatment. Particular attention will be paid to ascertaining immune reconstitution reactions in ART-naïve patients after starting ART.

Five millilitres of blood will be collected on days 3, 5, 7, 10, 12, and 14 of the study for creatinine and electrolytes. Full blood count (FBC) and alanine transaminases (ALT) will be obtained on days 7 and 14 of the study. On the day of the visit to the study clinic (week 4), blood will be drawn for creatinine, electrolytes, FBC and ALT. An extra 2.5 ml of blood will be taken for PK studies at the time of monitoring blood tests, on days 1 and 3 (excluding the single-dose arm) at the end of AmBisome infusion, and then 3, 6, 8 and 24 h post infusion. Follow-up CSF examinations will be performed on days 3, 7, 14 and 21 to determine opening pressure, quantitative fungal culture (QCC), CSF for drug levels, and immune parameters. In a variation on prior EFA studies (LPs on day 1, 7 and 14), in step 1 LP will be done at day 21 and for day-14 and day-21 quantitative cultures, an extra plate will be spread with 1 ml of undiluted CSF – this will increase sensitivity tenfold, and may help differentiate the duration of the effect of AmBisome on clearance with alternative regimens. Cryptococcal clearance rates will be calculated using a summary statistic for each patient, the rate of decrease in log CFU per ml CSF per day derived from the slope of the linear regression of log CFU against time for each patient. A linear regression model will be used to compare mean rates of decline or EFA for each experimental treatment, giving summary differences with 95 % CI and significance levels. We will adjust analyses for potential confounding factors, including baseline fungal load. Note that follow-up CSF examinations for study purposes in step 2 will be performed on days 7 and 14 only.

### Type of analysis

After data cleaning, analysis will proceed according to the predesigned analysis plan. The primary analysis (for both step 1 and step 2) will be intention-to-treat analysis. Note, in step 1, patients who die prior to day 3 will not have EFA calculated and thus, will be censored from EFA analysis (modified intention-to-treat analysis – prior experience of over 500 patients studied using this method suggests EFA data will be available in at least 90 % of patients). Linear regression models will be calculated for step 1. Mean rate of decrease in CSF cryptococcal CFU (EFA) will be the dependent variable and treatment group (using the standard treatment arm as a comparator) will be the primary independent variable. The comparator groups will be compared to the standard treatment arm for non-inferiority using standard criteria with an acceptable delta of 0.2 log_10_ CFU/ml/day.

Secondary analysis will include per-protocol analysis. Following a crude analysis, adjusted analysis will be performed including covariates that may influence outcome. As per the crude analysis, comparator groups will be compared to the standard treatment arm for non-inferiority using standard criteria with an acceptable delta of 0.2 log_10_ CFU/ml/day. Adjustment will be made for baseline fungal burden, which has been found to be associated with rate of clearance in previous studies, and for CD4 cell count, giving summary differences with 95 % CI.

The decision about which regimen will be taken forward from step 1 to step 2 will be taken by the TSC in conjunction with the DMC, and will be based upon predefined safety and minimal efficacy criteria laid down in the full statistical analysis plan. Briefly the shortest-course AmBisome regimen of: 1) AmBisome 10 mg/kg on day 1 (single dose), 2) AmBisome 10 mg/kg on day 1, AmBisome 5 mg/kg on day 3 (two doses), 3) AmBisome 10 mg/kg on day 1, AmBisome 5 mg/kg on days 3 and 7 (three doses), that demonstrates non-inferiority to the control arm in step 1 (in terms of EFA as defined above) will be considered for step 2. The ultimate decision will also take into account accrued safety, efficacy and mortality data and the results of PK/PD analysis. Whilst formal non-inferiority testing of EFA from step 1 will be the primary evidence used to inform the decision, the final choice of treatment arm will be at the discretion of the TSC.

Primary and secondary outcomes for step 1 and step 2 are as listed above. For step 2 the primary endpoint is mortality within the first 10 weeks by treatment arm. The two treatment groups will be compared using the Cochran-Mantel-Haenszel test for categorical data. Patients lost to follow up will be censored in the initial analysis. Sensitivity analysis in which all patients lost to follow up are assumed to have died, and Cox regression time-to-event analysis will be performed.

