### Sample size

Step 1: using a non-inferiority design, assuming an EFA of 0.50 log colony forming units (CFU)/d, with standard deviation of 0.25 in the standard daily dosing control arm, an acceptable delta of 0.2, one-sided alpha of 0.025 and 90 % power, gives a sample size of 33 patients per arm. A total sample of 40 patients per arm (160 patients in total) will therefore be planned to allow for patients who die prior to having a second lumbar puncture (LP) to allow for an EFA measurement. An interim analysis will be done after 20 patients per arm to make adjustments, if necessary, to the required sample size, or to consider stopping one or more arms if any are found to result in significantly lower EFA than the control arm (*p* <0.05) and are deemed unlikely to meet the predefined non-inferiority criteria outlined above if continued to completion.

Step 2: a non-inferiority design has been chosen for assessment of the primary mortality endpoint, as a short course of AmBisome is not expected to be superior to the standard course, but is expected to have similar efficacy, while being easier to administer, affordable, and better tolerated. Using a non-inferiority design assuming 10-week mortality of 25 %, with an acceptable non-inferiority margin of 15 %, one-sided α = 0.025 and 90 % power, gives a sample size of 176 per arm. Using the 40 patients already recruited into each of the control arm and the short-course AmBisome arm from step 1 chosen for step 2, 136 additional patients per arm are required. To allow for withdrawals and losses to follow up a sample size of 150 patients per arm is planned, giving a total sample size for step 2 of 300 patients.

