### Allocation

Patients will be randomised individually using a computer-generated programme. Randomisation lists and sealed envelopes will be prepared by an independent statistician in advance and sent to the sites. Randomisation will be stratified by abnormal mental status and ART status on admission at each site to ensure equal numbers of severely ill patients and patients on ART in each group. An allocation ratio of 1:1 and block sizes of 8 will be used. The study monitor will audit the randomization and allocation concealment process to ensure there are no violations [37].

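### The lead Step 1 comparison of EFA reads as crude: adjustment for baseline fungal load comes second, no stated model includes the stratification factors, and the deciding model is not named

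*Protocol article*

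**What the plan says.** Three sections of the Protocol article bear on this.

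- **Allocation:** "Randomisation will be stratified by abnormal mental status and ART status on admission at each site".
- **Type of analysis:** the Step 1 model is a linear regression with EFA as the outcome and treatment group as the main explanatory variable. No covariate is named there. The next paragraph, which opens with the per-protocol analysis as secondary, continues: "Following a crude analysis, adjusted analysis will be performed including covariates that may influence outcome". It then says: "Adjustment will be made for baseline fungal burden, which has been found to be associated with rate of clearance in previous studies", and adds CD4 count. The crude and the adjusted comparisons are both judged against the margin of 0.2.
- **Schedule:** analyses will be adjusted for potential confounders, baseline fungal load among them. The section does not say whether the adjusted result is the primary one.

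Type of analysis also makes the formal non-inferiority test of EFA the main evidence for choosing the Step 2 regimen.

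**The concern.** The protocol itself identifies a baseline variable that predicts the outcome, and it stratifies the randomisation on three others. The comparison that appears to lead uses none of the four.

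Two things follow. Any variance in EFA that these variables explain stays in the residual, so the confidence interval is wider than it needs to be. And with about 36 evaluable patients per arm, a chance difference in baseline load between arms goes uncorrected in the lead result.

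There is also a gap in the decision rule. Crude and adjusted results face the same margin, and nothing says which prevails if they disagree. Step 1 looks for the shortest non-inferior course, so the practical risk is that an acceptable short regimen misses the margin through avoidable noise, or that the choice between two results is made after both are known.

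**Working it through.** **Inputs from the Protocol article.** Sample size gives the planning values for EFA: "assuming an EFA of 0.50 log colony forming units (CFU)/d, with standard deviation of 0.25 in the standard daily dosing control arm". The same section supplies the margin (0.2), the one-sided α (0.025), the target power (90%), the resulting 33 per arm and the 40 per arm to be recruited. Type of analysis expects EFA data in at least 90% of patients, so about 40 × 0.9 = 36 evaluable per arm.

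**Assumed input.** R², the share of EFA variance explained by baseline load and the stratification factors together, is not in the documents. I use 0.1, 0.2 and 0.3, with 0 for the crude model.

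**Step 1. Reproduce the plan's figure.** n per arm = 2 × (1.960 + 1.282)² × 0.25² / 0.2² = 32.8, rounded up to 33. This matches. The planning SD is unadjusted, so the sample size takes no credit for covariates.

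**Step 2. Crude power at 36 per arm.** SE = 0.25 × √(2/36) = 0.0589. Power with no true difference = Φ(0.2/0.0589 − 1.96) = Φ(1.434) = 92.4%. At 33 per arm it is 90.1%. A noncentral t calculation gives 91.7% and 89.3%, so the normal approximation is adequate.

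**Step 3. Adjusted model.** Residual SD = 0.25 × √(1 − R²); the SE shrinks by the factor √(1 − R²); the equivalent crude sample is 36/(1 − R²). With a true deficit of 0.05, replace 0.2 by 0.15 in the power formula.

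| R² (assumed) | Residual SD | SE reduction | Equivalent n per arm | 95% CI half-width | Power, no true difference | Power, true deficit 0.05 |
|---|---|---|---|---|---|---|
| 0 (crude) | 0.250 | – | 36 | 0.1155 | 92.4% | 72.1% |
| 0.1 | 0.237 | 5% | 40 | 0.1096 | 94.7% | 76.5% |
| 0.2 | 0.224 | 11% | 45 | 0.1033 | 96.7% | 81.2% |
| 0.3 | 0.209 | 16% | 51 | 0.0966 | 98.2% | 86.0% |

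**Step 4. Chance imbalance in baseline load.** A one-standard-error difference in mean baseline load between two arms of 36 is √(2/36) = 0.236 baseline SDs. If baseline load alone explained R², that imbalance would move the crude EFA difference by √R² × 0.25 × 0.236 = √R² × 0.0589. This is 0.019, 0.026 or 0.032 log10 CFU/ml/day for R² of 0.1, 0.2 or 0.3, or about 9, 13 or 16% of the margin.

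**The case against.** The strongest reply is that this is detail for the SAP. The article points to a full analysis plan that is not shown. It calls treatment group the primary explanatory variable rather than the only one, and its phrase about covariates does not exclude the stratification factors. This stands in part: the SAP may already settle the matter. But the article does more than defer. It gives an order, crude then adjusted, and names an adjustment set, and both are choices that can be reviewed.

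Several stronger readings are tempting, and the documents do not support them.

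- **That baseline fungal load is ignored.** It is not. Type of analysis plans an adjusted non-inferiority comparison that includes it, and Schedule mentions the adjustment too. The question is which analysis leads.
- **That Step 1 is underpowered or wastes precision already bought.** The 33 per arm rests on the unadjusted SD, and the crude analysis delivers the planned power. The gain is forgone, not lost from the plan.
- **That omitting the strata makes the test invalid.** Leaving out balanced prognostic factors makes the interval too wide, which is conservative. Type I error is not inflated.
- **That the strata certainly matter.** Nothing in the article links site, mental status or ART status to EFA. If they do not predict it, adjusting for them gains nothing, and the benefit comes from baseline load alone.
- **That a wrong choice of regimen follows.** The Trial Steering Committee also weighs safety, clinical efficacy, mortality and PK/PD results, and has final discretion.
- **That Step 2 has the same flaw.** Type of analysis names a Cochran-Mantel-Haenszel test for mortality and Outcome measures plans an adjusted secondary analysis. No Step 2 defect is shown here.

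**Conclusion.** The point holds as a recommended improvement, not as an error in a stated figure. As the article reads, the lead Step 1 comparison is crude, no stated Step 1 model includes the stratification factors, and Schedule and Type of analysis leave open which model decides non-inferiority.

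The size depends on an R² that the documents do not give. Across the assumed range of 10 to 30%, the gain in power is about 2 to 6 percentage points if the arms are truly equal (94.7 − 92.4 = 2.3; 98.2 − 92.4 = 5.8). It is about 4 to 14 points if the short course is truly slower by 0.05 (76.5 − 72.1 = 4.4; 86.0 − 72.1 = 13.9). The second case is the more relevant one, because such a regimen lies well inside the margin and the crude analysis would miss it more than a quarter of the time. These figures assume an SD of 0.25 in both arms, 36 evaluable patients per arm and the normal approximation. They also ignore the few degrees of freedom that the covariates use.

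**What to change.** In Type of analysis, state that Step 1 non-inferiority is decided by the linear regression of EFA on treatment group, adjusted for baseline log10 CFU, site, mental status and ART status, with the 95% confidence interval set against the existing margin of 0.2. Report the crude difference as supportive. The model that also includes CD4 count can stay as a further secondary analysis. Make the sentence in Schedule refer to this same model, so that the two sections agree.

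The cost is wording in the protocol and the SAP. The stratification factors are known at randomisation and the baseline count is already needed for the planned adjustment, so no new data, visits or patients are required. The sample size can stay as it is. The change should be made before any EFA comparison by arm is seen, including the interim look at 20 patients per arm.

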### Choice of non-inferiority margin

Step 1: previous studies demonstrate that the EFA of 14-day high-dose amphotericin-based regimens is in the region of 0.5 log CFU/d [31], and it is anticipated that standard-dose AmBisome regimens will be similar. The acceptable delta of 0.2 log CFU/d was selected on the basis of combined EFA data from over 500 patients included in prior studies (Fig. 2) suggesting that notable increases in mortality are not seen until the EFA drops below 0.3 log CFU/d.

Step 2: we anticipate that short-course AmBisome will have the same 10-week mortality as standard 14-day courses. A non-inferiority margin of 15 % below an assumed efficacy of 75 % (based upon recent data from South Africa and Botswana [3, 28, 35]) was considered acceptable based on the clinical acceptability and feasibility of the novel short-course regimens compared to standard 14-day courses of AmBisome, the current limited availability of conventional Amphotericin B-based treatments in much of Africa, reported treatment outcomes with Amphotericin B monotherapy [36] and high-dose fluconazole monotherapy in Africa [5, 14], and considerations relating to achievable recruitment rate projections. The Data Monitoring Committee (DMC) will regularly review mortality data, and appropriate increases to sample size will be made should the mortality in the control arm prove to be higher than anticipated.

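### The one Step 2 primary analysis that the article states is a test of no association, and nothing in the analysis text ties it to the 15-point non-inferiority margin

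*Protocol article*

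**What the plan says.** **Design.** Under Sample size, Step 2, the Protocol article states that "a non-inferiority design has been chosen for assessment of the primary mortality endpoint". The calculation proceeds "assuming 10-week mortality of 25" per cent, with a 15% margin, and "one-sided α = 0.025 and 90 % power, gives a sample size of 176 per arm". Choice of non-inferiority margin adds that "we anticipate that short-course AmBisome will have the same 10-week mortality as standard 14-day courses" and describes "A non-inferiority margin of 15 % below an assumed efficacy of 75" per cent. The margin is therefore an absolute one: a floor of 60% survival, or 40% mortality.

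**Analysis.** The Step 2 primary analysis is described in one place, at the end of Type of analysis: "The two treatment groups will be compared using the Cochran-Mantel-Haenszel test for categorical data". The next sentence reads "Patients lost to follow up will be censored in the initial analysis". A sensitivity analysis counting losses as deaths and a Cox regression follow. That text contains no margin, no interval for the mortality difference and no criterion for declaring non-inferiority.

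**Contrast with Step 1.** The same section says, for both the crude and the adjusted Step 1 analysis, that arms are compared with control for non-inferiority with a delta of 0.2 log10 CFU/ml/day, and it mentions 95% confidence intervals.

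**The concern.** The Cochran-Mantel-Haenszel (CMH) test asks whether mortality and treatment are unassociated within strata, that is, whether the common odds ratio is 1. The Step 2 question is whether an excess of 15 points or more can be excluded. These are different null hypotheses. A non-significant CMH result can arise because the arms are similar or because the data are imprecise, and it does not say which. The other analyses named do not close the gap: counting losses as deaths changes the data rather than the hypothesis, and no margin is given on the hazard-ratio scale for the Cox model.

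At stake is the confirmatory conclusion of the trial. The article expects equal mortality in the two arms. If that is true, the usual CMH result will be a non-significant p value, and the article's analysis text does not say how to get from there to a statement about non-inferiority.

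A smaller wording problem sits beside it. A CMH test on a binary outcome cannot censor anyone. Patients lost to follow-up can only be left out of the table.

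**Working it through.** **Inputs from the Protocol article.** Mortality 25% in both arms, margin 15 points, one-sided alpha 0.025 and power 90% (Sample size; Choice of non-inferiority margin). Allocation is equal: "An allocation ratio of 1:1 and block sizes of 8 will be used". Forty patients per arm carry over from Step 1 and 150 per arm are planned in Step 2, giving 40 + 150 = 190 per arm (Sample size).

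**1. Reproduce the plan's own figure.** For a non-inferiority test on the risk difference with a true difference of zero:

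n per arm = 2 × p(1 − p) × (z₀.₉₇₅ + z₀.₉₀)² / margin²

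= 2 × 0.25 × 0.75 × (1.95996 + 1.28155)² / 0.15²

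= 0.375 × 10.507 / 0.0225 = 175.1, rounded up to **176**.

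This matches the article, and 176 − 40 = 136 matches its number of additional patients. The sample size is thus built for a test against an absolute 15-point margin. A two-sided 5% test of no difference, to detect 25% versus 40% with 90% power, would need 203 per arm.

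**2. Two rules compared.** All pairs of binomial outcomes were enumerated exactly, with control mortality 25%.

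- *Margin rule:* the upper limit of the two-sided 95% Wald CI for the mortality difference (short course minus control) is below 15 points.
- *Non-significance rule (hypothetical):* the short course is not significantly worse on a pooled two-sided 5% z test. This unstratified test stands in for CMH because the article gives no stratum rates.

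| True short-course mortality | n per arm | Passes margin rule | Not significantly worse |
|---|---|---|---|
| 25% (equal) | 176 | 90.2% | 97.5% |
| 25% (equal) | 190 | 92.2% | 97.5% |
| 35% (10 points worse) | 176 | 17.6% | 46.5% |
| 35% (10 points worse) | 190 | 18.6% | 42.9% |
| 40% (at the margin) | 176 | 2.5% | 14.5% |
| 40% (at the margin) | 190 | 2.4% | 11.8% |

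The margin rule delivers the planned operating characteristics: about 90% power at equality and about 2.5% error at the margin. The non-significance rule does not.

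**3. How often the two rules part.** At 190 per arm, the share of trials that are non-significant yet fail the margin is 5.2% under equality, 21.5% at a true 5-point excess and 24.4% at a true 10-point excess.

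**4. One example.** Take 44/176 control deaths and 56/176 short-course deaths. The difference is 31.8% − 25.0% = 6.8 points. Its standard error is √(0.25 × 0.75/176 + 0.318 × 0.682/176) = 0.0479, so the 95% CI is 6.8 ± 9.4, or −2.6 to 16.2 points. The pooled test gives p = 0.16. The test finds no difference, but a 15-point excess is not excluded.

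**The case against.** The strongest reply is that the article does prespecify a non-inferiority trial. The hypothesis, margin, alpha, power and rationale are all stated, and the sample size is correct for them. The article also says that analysis follows a predesigned plan, which is not shown. Strata, effect measure, interval method and declaration rule are details that a condensed article commonly leaves to such a plan. Nowhere does it say that a non-significant CMH result will be read as non-inferiority.

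Most of this stands, and it rules out stronger readings that a reader might infer:

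- *That the trial cannot answer its own question.* The data to be collected and the planned numbers permit the margin test without change.
- *That the margin will never be tested.* That could be said only after seeing the analysis plan.
- *That a regimen clearly outside the margin could readily pass.* At 190 per arm, no non-significant result has an observed excess above 10.0 points, so the point estimate is never beyond the margin. At a true excess of 20 points, non-significance occurs only 1.5% of the time (2.2% at 176).
- *That censoring is a serious separate flaw.* The Step 1 text uses the word for patients left out of the analysis of early fungicidal activity, so exclusion is the likely meaning here too, and a sensitivity analysis for losses is planned.

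What the reply does not remove is that the article goes beyond silence. It names a primary method, and that method's null hypothesis does not fit the stated design. The same section attaches the margin to the Step 1 analysis, so brevity alone does not explain its absence for the confirmatory endpoint. An analysis plan that copied the sentence would inherit the mismatch; one that set it right would depart from the published text.

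**Conclusion.** The point holds as a mismatch between stated method and stated design. The only Step 2 primary analysis in the article tests no association and is not linked to the 15-point margin at one-sided 0.025 on which the 176 per arm rest. By itself it cannot establish non-inferiority.

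The size depends on how the result would be read. If non-significance were taken as success, the chance of passing a regimen exactly 15 points worse would be about 12% at 190 per arm, or 14.5% at 176, instead of 2.5%. For a regimen 10 points worse it would be 43% instead of 19% at 190 per arm. These figures assume 25% control mortality, no losses at the stated numbers and an unstratified test. Stratification would move them slightly but would not change the hypothesis tested. They describe a reading that the article leaves open, not one that it prescribes, and the unseen analysis plan may already exclude it.

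**What to change.** In Type of analysis, replace the Step 2 test sentence with wording to this effect:

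> The primary analysis is the absolute difference in 10-week mortality (short course minus control), estimated as a Mantel-Haenszel risk difference stratified by the randomisation factors. Non-inferiority is concluded if the upper limit of the two-sided 95% confidence interval is below 15 percentage points.

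Keep the CMH p value, the analysis counting losses as deaths and the Cox regression as supportive. For the binary analysis, say that patients lost to follow-up are excluded, not censored. Check that the analysis plan carries the same rule.

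The cost is wording only. The data collected and the 176 per arm are unchanged, as are the 150 per arm to be recruited in Step 2. With the margin rule, exact power at equal mortality is 90.2% at 176 per arm and 92.2% at 190.

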### Consent

Written informed consent to enter into the trial must be obtained from participants, or in the case of those with mental obtundation, from the patient’s guardian or a person with legal responsibility, after explanation of the aims, methods, benefits and potential hazards of the trial and before any trial-specific procedures are performed or any blood is taken for the trial. In the case of patients with altered mental status enrolled into the study, consent will be obtained as above as soon as the patient’s mental status improves, with care taken to ensure they understand that they are free to withdraw from the study and if they do so this will not jeopardise their immediate and future care. Participants who withdraw will revert to standard of care at the recruiting site (usually amphotericin B deoxycholate and fluconazole 800 mg daily for 2 weeks, or fluconazole 1,200 mg daily for 2 weeks). It will be made completely and unambiguously clear that the participant (or guardian) is free to refuse to participate in all or any aspect of the trial, at any time and for any reason, without incurring any penalty or affecting their treatment (or that of their guardian). Signed consent forms will be kept by the investigator and documented in the case report form (CRF) and a copy given to the participant or family.

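### Step 2 primary mortality analysis: lost patients are to be censored in a categorical test that has no censoring, so they are in effect excluded from an analysis labelled intention-to-treat

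*Protocol article*

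**What the plan says.** All of the following is in the protocol article, mostly under Type of analysis.

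- Population: "The primary analysis (for both step 1 and step 2) will be intention-to-treat analysis".
- Step 2 endpoint: "For step 2 the primary endpoint is mortality within the first 10 weeks by treatment arm".
- Test: "The two treatment groups will be compared using the Cochran-Mantel-Haenszel test for categorical data".
- Lost patients: "Patients lost to follow up will be censored in the initial analysis".
- Further analyses: "Sensitivity analysis in which all patients lost to follow up are assumed to have died, and Cox regression time-to-event analysis will be performed".
- Use of the same word in Step 1: "patients who die prior to day 3 will not have EFA calculated and thus, will be censored from EFA analysis". The article labels that Step 1 set modified intention-to-treat. It gives no such label for Step 2.

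Under Sample size, Step 2 needs 176 per arm. Of these, 40 come from Step 1, which leaves 136 new patients. The article then says: "To allow for withdrawals and losses to follow up a sample size of 150 patients per arm is planned".

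**The concern.** A Cochran-Mantel-Haenszel test works on a table of dead and not dead. A patient whose 10-week status is unknown must be given a status or left out. The article's own Step 1 usage of *censored* means left out, so the natural reading of the Step 2 rule is a complete-case analysis. I take the initial analysis to be the primary one, because the others are introduced as sensitivity or additional analyses.

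Two things follow. A patient last seen alive in week 9 contributes nothing, while one who died in week 2 counts in full. And the named population (everyone randomised) is not the population that the stated rule produces.

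This matters because the phase III conclusion is a non-inferiority claim on a mortality difference. If loss is related to prognosis, and differently so in the two open-label arms, exclusion can move the estimate towards or away from the margin.

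**Working it through.** **1. The plan's own figure.** Mortality is 25% in both arms, margin 0.15, one-sided alpha 0.025, power 90% (Sample size).

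n = (1.960 + 1.282)² × 2 × 0.25 × 0.75 / 0.15² ≈ 175.1, so 176 per arm. The stated figure is reproduced.

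**2. The allowance.** Randomised per arm: 40 + 150 = 190. Spare: 190 − 176 = 14. Then 14/190 = 7.4% of the arm (14/150 = 9.3% of the new patients). The article states no loss rate; this is what its numbers imply for withdrawals and losses together.

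**3. Shift in the difference from leaving out the lost.** Let retained patients have 25% mortality in both arms, so that the complete-case difference is 0. Let a fraction L = 14/190 be lost in each arm, with mortality q1 and q2 among the lost. The difference in all randomised patients is then L × (q1 − q2).

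- 50% v 25%: 0.0737 × 0.25 = 1.8 points (12% of the margin)
- 60% v 25%: 0.0737 × 0.35 = 2.6 points (17%)
- all dead v all alive: 0.0737 × 1 = 7.4 points (49%)
- at 2% loss, 60% v 25%: 0.02 × 0.35 = 0.7 points (5%)

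The 50% and 60% are assumptions. They borrow the article's figures for fluconazole-based care (Background, Discussion). The article gives no mortality for lost patients.

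**4. What this can do to the decision.** Take 44/176 deaths observed in each arm, with 14 lost per arm (95% CI = difference ± 1.96 × SE, unpooled):

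- Lost excluded: 0 points (−9.05 to 9.05). Non-inferior.
- All lost counted as dead, as planned: 58/190 v 58/190, 0 points (−9.26 to 9.26). Non-inferior.
- Lost short-course dead, lost controls alive: 58/190 v 44/190, 7.37 ± 8.88 points (−1.51 to 16.25). Fails the margin.

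**5. False non-inferiority when the true difference equals the margin (40% v 25%, 190 per arm).** Retained mortality in an arm is (p − Lq)/(1 − L). For 60% v 25% among the lost: (76 − 8.4)/176 = 38.4% and (47.5 − 3.5)/176 = 25.0%, a difference of 13.4 points. The probability of declaring non-inferiority is Φ((0.15 − difference)/SE − 1.96).

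| Loss (short v control) | Mortality among lost | Excluded: difference, error | All lost dead: difference, error |
|---|---|---|---|
| none | – | 15.0, 2.5% | 15.0, 2.5% |
| 7.4% v 7.4% | 40% v 25% (random loss) | 15.0, 2.5% | 13.9, 4.1% |
| 7.4% v 7.4% | 60% v 25% | 13.4, 5.1% | 12.4, 7.6% |
| 7.4% v 7.4% | 60% v 60% | 16.2, 1.4% | 15.0, 2.5% |
| 10% v 5% | 60% v 60% | 14.6, 3.0% | 17.0, 0.9% |
| 2% v 2% | 60% v 25% | 14.6, 3.0% | 14.3, 3.5% |

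The all-lost-dead rule guards against unequal loss (fifth row). When loss is equal but prognosis among the lost differs by arm, it does worse than exclusion (third row).

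**The case against.** The strongest reply has three parts.

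*The plan already tests this.* The sentence after the quoted rule adds an all-lost-dead analysis and a Cox regression, and the Cox model does use follow-up up to last contact. That is real but partial protection. The all-lost-dead rule treats both arms alike and can hide a difference (step 4). The Cox model gives a hazard ratio, not the risk difference to which the 15-point margin applies, and it assumes non-informative censoring.

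*The effect may be small.* The Schedule section plans telephone tracing and travel support for complete 10-week data. At 2% loss the error rate is 3.0% against 2.5%, and in some patterns exclusion is conservative. This stands, and it limits the size of the point.

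*An article is condensed, and the details belong in the analysis plan.* That would answer an omission. Here the article states both the test and the rule, and the two do not fit.

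A reader might infer more than the text supports:

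- *Withdrawn patients are also dropped.* The rule names only patients lost to follow-up. The Sample size section groups withdrawals with losses, which suggests that both were expected to be unevaluable, but an enrolment allowance is not an analysis rule.
- *Changing drugs at withdrawal biases the comparison.* The Consent section says "Participants who withdraw will revert to standard of care at the recruiting site". That is compatible with intention-to-treat if vital status is still collected.
- *Short-course patients leave earlier, so loss must differ by arm.* Schedule has daily monitoring for at least two weeks in every arm and sets the same Step 2 lumbar puncture days for both arms. The shorter hospital stay in the Discussion is a hoped-for future benefit.
- *The Consent section contradicts itself on treatment after refusal.* It is ordinary no-penalty wording beside a statement of the care that follows withdrawal.

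**Conclusion.** The point holds for patients lost to follow-up. The rule cannot be carried out in the named test as written. On the article's own usage it means exclusion, and the result is a complete-case analysis under an intention-to-treat label.

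The size is moderate and conditional: 1.8–2.6 points of the 15-point margin if the whole 7.4% allowance is lost and mortality among the lost is 50–60% in one arm and 25% in the other, with 7.4 points as the outer bound. Loss by arm and mortality among the lost are assumptions, so the documents do not show which arm would be favoured, nor that bias will occur. The sample size of 176 per arm is not in question.

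**What to change.** In Type of analysis, Step 2:

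1. Replace the censoring sentence. Analyse every randomised patient in the assigned arm, using the stratified difference in Kaplan-Meier 70-day mortality with its 95% CI compared with the 15-point margin. Lost patients then contribute up to last contact.
2. State that patients who stop trial treatment stay in vital-status follow-up to day 70 unless they refuse it, through the tracing already described under Schedule. This step does most to reduce bias, because it reduces the missing outcomes themselves.
3. Kaplan-Meier also assumes non-informative censoring, so add a sensitivity analysis counting lost short-course patients as dead and lost controls as alive, beside the two analyses already planned.
4. If exclusion is kept instead, call the Step 2 primary analysis modified intention-to-treat, as Step 1 does.

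The cost is a few sentences, one standard analysis and some calls to patients who stopped treatment. No extra patients are needed: with 190 per arm the normal-approximation power is 92.2% if all outcomes are known and 90.1% if 14 per arm are lost at random.
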